#### **10.2.4 Urgent safety measures**

In accordance with the principles of GCP as laid out in ICH E6, the investigator(s) has/have primary responsibility for assuring participant safety throughout the performance of study procedures. An urgent safety measure is defined as any measure which an investigator may need to implement which is a deviation from, or a change in, the protocol to eliminate an immediate hazard(s) to trial participants without prior IEC/IRB approval/favourable opinion.

The investigator may take appropriate urgent safety measures to protect the participants of a clinical trial against any immediate hazards to their health or safety. However, the investigator must inform the Sponsor/CRO within 24 hours of having taken such measures.

The Sponsor shall immediately, and in any event, no later than 3 days from the date the measures are taken, give written notice to the licensing authority and the relevant IEC/IRB of the measures taken and the circumstances giving rise to those measures.

All urgent safety measures must be reported to the Sponsor/CRO by using the SAE contact numbers provided in the Investigator’s Trial File within 24 hours of having to take such a measure(s). Such reports can be initiated by telephone but must be officially documented by the investigator (by email or fax) and must include details of what measures were taken and the circumstances giving rise to those measures.

#### **10.2.5 Pregnancy reporting**

This process is aimed at ensuring the appropriate monitoring of the potential risk related to IMP exposure of pregnant women and/or foetuses as well as the risks associated with exposure

of a father, regarding congenital abnormalities or birth defects in their offspring. It also ensures compliance with applicable international and local regulations.

The requirements are applicable to all participants following exposure to IMP.

**Female trial participants:** The trial participant must be advised by the investigator to inform the investigator immediately if the participant suspects she may be pregnant. Any pregnancy that occurs within 72 hours after administration of the IMP should be reported to the investigator.

**Male trial participants:** The trial participant must be advised by the investigator to inform the investigator immediately if the participant suspects that his partner became pregnant after the he was administered with IMP. Any pregnancy that occurs in a partner of the male participant within 72 hours after administration of the IMP should be reported to the investigator.

When a trial participant reports a pregnancy (post-IMP administration) to the investigator, a pregnancy test should be arranged for the trial participant (or his partner) by the investigator within 7 days of the pregnancy being reported.

The investigator must inform the Sponsor within 24 hours of receiving positive pregnancy test results by using either a copy of the relevant CRF page (demography or AE) or via email. The investigator should include an estimated date of conception when communicating with the Sponsor/CRO.

### **10.3 Other Variables**

#### **10.3.1 Demographic data**

The following demographic data will be recorded during the baseline visit:

- Age
- Height
- Weight
- Sex
- Race

#### **10.3.2 Medical and surgical history**

The medical and surgical history will be recorded during the screening visit.

#### **10.3.3 Pre-treatment events**

Events that occur before administration of IMP will be recorded as medical or surgical history in the eCRF.

The following information on pre-treatment events will also be recorded in the eCRF:

- The onset time
- Action taken

- Status
- Intensity

#### **10.3.4 Prior and concurrent medication**

Prior and concurrent medications will be recorded during the screening visit, at the time of imaging, at T2, and at T3.

#### **10.3.5 Vital signs**

Vital signs (blood pressure, heart rate, respiratory rate, temperature, respiratory rate) will be monitored at the screening visit (see [Table 1](#)).

#### **10.3.6 Physical examination**

The managing physician will conduct physical examinations during the screening visit. The physical examination and neurologic examination will include recording an assessment as needed for determination of the inclusion/exclusion criteria.

#### **10.3.7 Cognition/functioning**

The investigator can use the neuropsychological tests that are normally used in each centre. Data on each participant's cognition/functioning (episodic memory, verbal memory, attention, verbal fluency, visual/spatial function, executive function) will be recorded at T0, T2, and T3.

#### **10.3.8 MRI and CT results**

As part of the inclusion criteria, the participant must have undergone MRI and CT imaging up to 12 months before the screening visit, to rule out intracranial masses or other lesions as causes of their symptoms. The results of this MRI and CT imaging will be recorded in the eCRF at T0, after the Informed Consent form has been signed.

#### **10.3.9 Mini-Mental State Examination**

The score of the Mini-Mental State Examination at T0, T2, and T3 will be recorded in the eCRF.

#### **10.3.10 ICECAP-O (ICEpop CAPability measure for Older people)**

The score of the ICECAP-O at T0, T2, and T3 will be recorded in the eCRF.

### **10.3.11 Brief-COPE**

The score of the Brief-COPE at T0, T2, and T3 will be recorded in the eCRF.

### **10.3.12 EQ-5D-5L (5 level-EQ-5D)**

The score of the EQ-5D-5L at T0, T2, and T3 will be recorded in the eCRF.

### **10.3.13 Hospital Anxiety and Depression (HAD)**

The score of the HAD scale at T0, T2, and T3 will be recorded in the eCRF.

### **10.3.14 Patient questionnaire (use of medical resources)**

Data from the patient questionnaire on the use of medical resources will be collected at T0, T1, T2, and T3 and recorded in the eCRF. (T1 does not require a clinic visit.)

In those centres where the participants in the Early Amyloid PET arm receive a diagnostic workup in addition to clinical evaluation before baseline, the relative costs will not be considered if the results of those exams are not known by the managing physician before the managing physician makes the etiologic diagnosis.

### **10.3.15 Syndromic diagnosis**

The syndromic diagnosis made by the managing physician (see section 7.5) at T0, T1, T2, and T3 will be recorded at in the eCRF.

### **10.3.16 Etiologic diagnosis**

The etiologic diagnosis made by the managing physician at T1, T2, and T3 will be recorded in the eCRF. Earlier on in the workup, when diagnostic hypotheses are made, up to 4 diagnostic hypotheses will be recorded.

### **10.3.17 Management plan**

The management plan (pharmacologic and nonpharmacologic) made by the managing physician at T1, T2, and T3 will be recorded in the eCRF. Pharmacologic management may include cognitive enhancers (acetylcholinesterase inhibitors, memantine, ginkgo biloba, and others [including nutraceuticals]), selective serotonin reuptake inhibitors, benzodiazepines, hypnotics, and neuroleptics (typical and/or atypical). Nonpharmacologic management may include cognitive rehabilitation, validation therapy, psychoeducation of family members, nutritional intervention, physical activity programmes, occupational therapy, and others.

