### 4.1.3 AMYPAD Diagnostic and Patient Management Study

To identify the optimal window of opportunity for possible intervention in the A $\beta$  pathway, researchers must establish in detail the sequence of events on the path towards AD.

This study will select and follow up a memory clinic population suspected of possible AD, focusing on those with subjective cognitive decline plus (SCD Plus), mild cognitive impairment (MCI), and dementia, to determine the utility of amyloid PET imaging with regards to change in diagnosis, diagnostic confidence, decision trees, and alterations between planned and actual patient management plans.

Through a European network of diagnostic memory clinics and affiliated PET centres, we will determine:

- Impact on diagnostic thinking and patient management
- Impact on diagnostic confidence and decision making
- Impact on patient reported outcomes
- Clinical utility of amyloid PET imaging in preclinical phases of AD (patients with SCD Plus)
- Costs and cost-effectiveness of early adoption vs late adoption of amyloid PET imaging
- Standardised methods of image quantitation across the PET tracers in order to perform pooled analysis across the AMYPAD program

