## **8.6 Prior and Concurrent Therapy**

Prior medication refers to medication taken within 4 weeks before injection of the study drug. Concomitant medication refers to medication received by the participant from the time of injection of the study drug.

In this study, there are no restrictions on prior and concomitant medications.

Any medications taken by the participant within 4 weeks before and up to the end of the observation period will be recorded in the eCRF along with the indication and dosage. Either the generic or the trade name may be recorded. The Sponsor/CRO will encode all therapy and medication according to a current well-recognised dictionary of medical codes.

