|                                                                                 |   |                |                |                |                |                |                |   |   |
|---------------------------------------------------------------------------------|---|----------------|----------------|----------------|----------------|----------------|----------------|---|---|
| Managing physician's etiologic diagnosis                                        |   | X              |                | X              | X              |                | X              |   | X |
| Managing physician's management plan                                            |   |                |                | X              | X              |                | X              |   | X |
| Managing physician's diagnostic confidence                                      |   | X              |                | X              | X              |                | X              |   |   |
| Randomisation d                                                      |   | X              |                |                |                |                |                |   |   |
| Amyloid PET imaging e                                                |   |                | X f |                |                | X g |                | X |   |
| Managing physician's estimate of the likelihood that the symptoms are due to AD | X | X              |                | X              | X              |                | X              |   |   |
| Adverse events h                                                     |   |                | X              | X              | X              | X              | X              |   | X |
| Amyloid PET scan results i                                           |   | X i |                | X i | X i | X i | X i |   | X |
| FDG-PET                                                                  |   | (X)            |                | (X)            | (X)            |                | (X)            |   |   |
| SPECT                                                                    |   | (X)            |                | (X)            | (X)            |                | (X)            |   |   |

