### **9.3 Amyloid PET Imaging for Participants in Early Amyloid PET Arm (≤4 Weeks After Baseline)**

All female participants of childbearing potential must have a negative pregnancy test before the imaging study is done.

The participants in the Early Amyloid PET arm of the study will undergo amyloid PET imaging within 4 weeks after baseline.

If the managing physician chooses to order amyloid PET imaging for the participants in the Free Choice arm, those participants may undergo the imaging at any time from baseline to 12 months after baseline.

The following will be recorded for all participants who have undergone amyloid PET imaging:

- Amyloid PET scan results
- All AEs that occur within 48 hours of study drug administration
- All SAEs occurring within 30 days of study drug administration
- Review of concurrent medications

Amyloid PET will be carried out with high priority for early amyloid PET arm patients.

.

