#### 10.1.2 Secondary endpoints

The timepoints are defined as follows:

- T0 = baseline,
- T1 = 12 weeks after T0,
- T2 = 6 months ( $\pm 14$  days) after T0,
- T3 = 13 months ( $\pm 4$  weeks) after T0;
- T4 =  $\leq 28$  days after the optional second scan, which will be 12 to 18 months after T0.

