##### 10.1.2.2 Patient management

- The difference between arms (Early Amyloid PET arm, the Late Amyloid PET arm, or the Free Choice arm) in the number of patients randomised to disease-modifying drug (DMD) or any other AD clinical trial at T2.
- The difference between the Early Amyloid PET arm and the Late Amyloid PET arm in number of participants with changes in the management plan (changes in or start of a new program or pharmacologic treatment) at T1 vs T2 vs T3.

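### The management plan is first recorded at week 12, after the Early arm's PET but before the Late arm's, and the plan-change endpoint names no reference for a change at T1

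*Protocol*

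**What the plan says.** On recording, Protocol section 10.3.17 states: "The management plan (pharmacologic and nonpharmacologic) made by the managing physician at T1, T2, and T3 will be recorded in the eCRF". The list of baseline items in section 9.2 contains no management plan. In Table 1 the row "Managing physician's management plan" is empty at screening and T0 and marked at T1, T2, T3 and T4 (T4 only after the optional second Early scan). The physician's other judgements in that table (syndromic diagnosis, etiologic diagnosis, confidence, likelihood of AD) all have a baseline mark.

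On timing, section 9.3 says: "The participants in the Early Amyloid PET arm of the study will undergo amyloid PET imaging within 4 weeks after baseline". Section 10.1.2 defines "T1 = 12 weeks after T0". Section 9.6 places the Late scan at 8 months (±8 weeks) and requires it to follow the T2 visit. Sections 6.1.1 and 9.7 make the T3 visit optional.

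On the endpoint, section 10.1.2.2 (also the Synopsis and section 12.6.1.2) compares how many people in Early and in Late meet this description: "participants with changes in the management plan (changes in or start of a new program or pharmacologic treatment) at T1 vs T2 vs T3". It gives no T0 reference and does not say what a change at T1 is measured against.

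**The concern.** The first recorded plan is post-PET in one arm and pre-PET in the other. A change counted between recorded plans therefore starts after the scan in Early and before it in Late. Randomisation does not correct this, because the asymmetry arises after randomisation from when the form is filled in.

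Impact on patient management is a named secondary objective (section 5.4.2.2), and section 4.1.3 describes the interest as "alterations between planned and actual patient management plans", which presupposes a plan written before the scan. Read in the wrong way, the data could lead the report to say that early PET produces no more, or even fewer, management changes than late PET, when the pattern comes from the recording schedule. Later analysis cannot recover a plan that was never recorded, and this matters most for non-drug care.

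**Working it through.** The Protocol gives no expected rate and no power figure for this endpoint. Section 12.7 covers the primary endpoint only. There is thus no stated figure to reproduce, and the check has two steps.

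**Step 1. Order of plan records and scans**

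| | Early | Late |
|---|---|---|
| PET | weeks 0 to 4 (9.3) | 8 months ±8 weeks, after T2 (9.6) |
| Plan records before PET | 0 | 2 (T1, T2) |
| Plan records after PET that the endpoint uses | 3 (T1, T2, T3) | 1 (T3, optional) |

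The first Early plan record comes at least 12 − 4 = 8 weeks after the scan.

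**Step 2. What the recorded contrasts would show (illustration on assumed rates)**

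Assumptions, none taken from the Protocol:
- Background change is b = 10% in each of the intervals T0–T1, T1–T2 and T2–T3.
- PET causes a change in c = 20% of scanned patients, equally in both arms.
- All Early-PET changes are made before T1.
- Everyone attends T3.

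The probability of at least one change is 1 minus the product of the no-change probabilities.

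| Interval | Early | Late | Early − Late |
|---|---|---|---|
| T0–T1 (no T0 record exists) | 1 − 0.9×0.8 = 28.0% | 10.0% | +18.0 points |
| T1–T2 | 10.0% | 10.0% | 0 |
| T2–T3 | 10.0% | 1 − 0.9×0.8 = 28.0% | −18.0 points |
| T1–T3 | 1 − 0.9² = 19.0% | 1 − 0.9²×0.8 = 35.2% | −16.2 points |
| T0–T3 | 1 − 0.9³×0.8 = 41.7% | 41.7% | 0 |

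In general the T0–T1 difference is +(1−b)c and the T1–T3 difference is −(1−b)²c. Over b = 5 to 20% and c = 10 to 30%:
- T0–T1 runs from 0.80×0.10 = +8 points to 0.95×0.30 = +28.5 points.
- T1–T3 runs from −0.80²×0.10 = −6.4 points to −0.95²×0.30 = −27.1 points.

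**Sensitivity to delay.** Suppose a share s of Early-PET changes is made only after T1. The Early T1–T3 rate becomes 1 − (1−b)²(1−sc). With b = 10% and c = 20%:
- s = 25%: 1 − 0.81×0.95 = 23.1%, against 35.2% Late.
- s = 50%: 1 − 0.81×0.90 = 27.1%, against 35.2% Late.

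The gap narrows but keeps its sign. The T0–T1 Early rate falls too, to 1 − 0.9×(1 − 0.75×0.20) = 23.5% and 1 − 0.9×(1 − 0.50×0.20) = 19.0%, against 10.0% Late.

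The T0–T3 row shows that a baseline record alone is not enough. Once both arms are scanned, equal effects cancel. The informative randomised contrast is T0–T1, when only Early has been scanned.

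**The case against.** The strongest reply is that the endpoint also counts starts of a new programme or drug. A start noted at T1 can be read as anything begun by week 12. Section 12.6.1 plans cross-sectional comparisons between arms at T1, by chi-squared test for a dichotomous endpoint. At T1 Early has been scanned, Late has not, and the arms are randomised, so that comparison would carry the Early PET effect. This stands, and it rules out the stronger inference a reader might draw, that the endpoint cannot see Early-PET changes at all. What remains is that the form, as described, captures the plan and not what it replaced. Comparing plan content at T1 is fair between arms, but it is not a count of participants whose plan changed, because starts in some patients can offset stops in others.

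Second, some pre-PET data exist:
- Medications are recorded at screening and on the imaging day (sections 9.1 and 10.3.4, Table 1), which gives a partial drug baseline.
- For programmes, section 10.3.14 says the resource-use questionnaire is collected at T0, and section 5.4.2.2 counts programmes as resource use. But Table 1 has no T0 entry for it, so the only possible non-drug baseline is itself uncertain.
- Section 6.1.1 records the plan's effective date at T1, which dates the plan without showing its predecessor.

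Third, a reader might infer that the Late arm's whole PET effect is captured. It is not. Only attenders of the optional T3 contribute, and section 12.5.3 restricts change analyses to complete cases. Nor is the T1–T2 contrast exactly zero in practice, since Early changes made after T1 would appear there.

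A reader might also see a defect in section 8.6, where "Concomitant medication refers to medication received by the participant from the time of injection of the study drug", since the scan falls at different times in the two arms. Those labels enter no management endpoint and remove no drug from the record, so nothing follows from them here. Finally, section 4.1.3 is background text and defines no endpoint.

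**Conclusion.** The point holds as a conditional one. No plan is recorded before Early PET, two are recorded before Late PET, and the endpoint does not say what a change at T1 is measured against. If change is taken between recorded plans, the Early-versus-Late contrast can be near zero or reversed although PET acts equally in both arms. If it is taken as starts by T1, the contrast is usable but lacks a documented baseline, most clearly for non-drug programmes.

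The direction follows from the schedule, provided that a good part of Early-PET changes are made before T1. The size does not come from the Protocol. Under the assumed 10% and 20% rates it is about −16 points for T1–T3 where T0–T1 would show about +18, and selective T3 attendance could move the former either way.

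This should be fixed, but it concerns one secondary endpoint. The primary endpoint and the power figures in section 12.7 are untouched.

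**What to change.** 1. Add the management plan, drug and non-drug, to the V0/T0 column of Table 1 and to sections 9.2 and 10.3.17, to be completed before randomisation.
2. In the Synopsis and sections 10.1.2.2 and 12.6.1.2, define the endpoint as change from T0 at T1, T2 and T3. Name T0 to T1 as the main Early-versus-Late contrast, because only the Early arm is scanned by then.
3. Reconcile section 10.3.14 with Table 1 on whether resource use is collected at T0.

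Section 8.6 needs no change for this purpose.

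The cost is one existing form repeated at a visit that already takes place, plus amended wording. For anyone enrolled before the change, screening medication can stand in for the drug part of the T0 plan. The non-drug part would stay missing unless a T0 resource-use record exists. If a T0 form cannot be added, the least that is needed is a stated reference for a change at T1, with contrasts between recorded plans not presented as the effect of early PET.

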### **10.3.18 Diagnostic confidence**

The managing physician's diagnostic confidence, as measured by a Visual Analogue Scale (0% meaning zero confidence in the diagnosis and 100% meaning complete confidence that the diagnosis is correct) at T0, T1, T2, and T3 will be recorded in the eCRF.

### **10.3.19 The managing physician's estimate of the likelihood that the patient's symptoms are due to AD**

The managing physician will be asked to evaluate, in percentage (0% to 100%), the likelihood that the patient's symptoms are due to AD.

### **10.3.20 Amyloid PET scan results**

The results of the amyloid PET scan will be recorded in the eCRF after the scan. The results of the visual reading will be recorded as positive or negative for the overall read. The timing of the scan is different for the different arms of the main study.

- **Early Amyloid PET arm:** participants will undergo amyloid PET scanning within 4 weeks of baseline. The participants in this arm will undergo an optional second scan 12 to 18 months after the first scan.
- **Late Amyloid PET arm:** participants will undergo amyloid PET scanning at 8 months  $\pm$  8 weeks.
- **Free Choice arm:** participants may or may not undergo amyloid PET scanning, according to the managing physician's decision. If they undergo scanning, the scan may take place at any time within 12 months after baseline.

### **10.3.21 FDG-PET**

FDG-PET imaging is not required under this protocol. If a participant undergoes FDG-PET scanning during this study, the results will be recorded in the eCRF.

### **10.3.22 SPECT imaging**

SPECT imaging is not required under this protocol. If a participant undergoes SPECT imaging of the brain during this study, the results will be recorded in the eCRF.

### **10.3.23 Cerebrospinal fluid (CSF) analysis**

Analysis of CSF is not required under this protocol. If such analysis is performed during this study, the results will be recorded in the eCRF.

